## **6.6 Expected Duration of Trial**

The trial is expected to last 12 months from the first participant's first visit to the last participant's last follow up visit. From signing consent to completing participation in the trial, each participant will be on study for approximately three weeks.

## **7.1 By Visit**

Participants will attend for a maximum of 6 study visits, depending on randomisation arm. Once screened, the remaining four visits will take place over a one-two week period. The schedule of assessments is summarised in separate visit schedules for each group. Reimbursement for time and transport will occur at each visit. A description of the visits is listed below.

### **7.1.1 Screening Visit**

Prior to the screening visit participants will be provided with written information about the trial in the form of a participant information sheet and will be allowed adequate time for questions and to consider the trial before agreeing to participate. It will be the responsibility of the investigator or designee to obtain written informed consent and assent where applicable, prior to undertaking any procedures detailed in the protocol.

The investigator or designee must provide adequate explanation of the aims, methods, objectives and potential risks and benefits of the trial. It must also be explained to the participant that they are free to refuse or withdraw from the trial for any reason without detriment to their future care or treatment.

Willing participants will be required to read, sign and date an informed consent document prior to any trial related procedures being performed. All willing participants will have to demonstrate that they have understood the information before they sign. In the case of those who are illiterate, the

informed consent document will be read to the participant in the presence of an independent witness. The participant thumbprints will then be documented as consent while the witness and staff will countersign. Participants will be given the opportunity to ask questions regarding the trial at any time during the trial period.

All participants less than 18 years old will be required to provide parental consent for participation in clinical research. All participants will be reimbursed for their travel expenses for all scheduled visits.

Screening evaluations will be used to determine the eligibility. Following informed consent, the screening visit will evaluate:

- Physical examination including measurement of weight, height, and vital signs (temperature, blood pressure)
- Assessment of concomitant medications
- Prior medical history
- Current symptoms - both systemic and those related to the genito-urinary tract
- Blood drawn for haemoglobin levels
- HIV testing using two point of care HIV tests (POCT). Any volunteers found to be infected with HIV-1 at screening will be referred for management according to local standard of care (section 7.2)
- Clinical eligibility for circumcision assessed using local VMMC guidelines.

For subsequent visits, participants will be requested to attend the research unit at a specified time based on their randomisation arms and dosing schedules.

### **7.1.2 Randomisation visit**

Once eligibility has been confirmed randomisation will take place. Consecutive sealed randomisation envelopes with study ID's printed and containing the allocated arm will be used (Section 6.4). After each randomisation, the participant ID and the allocated trial arm will be entered into a Log. This will be checked each week against the randomisation list prepared by the Trial Statistician.

For men allocated to randomisation arm 1, the control arm (no PrEP dosing), VMMC can occur on that day or up to 21 days following randomisation. For men allocated to randomisation arms

2-9 (PrEP dosing), PrEP dosing can occur up to 21 days following randomisation.

For men allocated to Arms 2-9 (PrEP dosing), DOT PrEP will be administered at the clinic. DOT entails a nurse overseeing the receipt and ingestion of study medication and documenting in the source document the time, the dose, and that the dose was ingested by the participant. The VMMC must occur up to 21 days following randomisation. Subsequent visits will be arranged according to randomisation group.

At the day of randomisation, all participants will also complete a self-or interviewer administered socio-behavioural survey and a short willingness to participate survey, which will include the following sections: socio-demographics, sexual behaviour, reasons to participate in the trial, attitudes towards PrEP and HIV prevention preferences. The survey will be translated into the main local languages of each country (South Africa: Zulu, Sesotho; Uganda: Luganda). All participants will complete this interviewer-administered and structured survey, using the electronic database, iDatafax. The survey will last approximately 20 minutes and will be accessed using a tablet, desktop computer or laptop. Surveys will be completed as part of the study procedures on the day of randomisation in a private room at the research sites.

A 9ml blood sample will be taken for research

### ***7.1.3 DOT PrEP dosing visits +/-1 hour of expected next dose***

The following evaluations will take place prior to next dose:

- AE review. If significant adverse events have been reported, these will be clinically followed in accordance to the instruction of the study physician.
- Concomitant medications review

### ***7.1.4 VMMC sample collection visit***

The following evaluations will take place prior to VMMC and the time of sample collection will be accurately recorded:

- Physical / genital exam if clinically indicated
- Concomitant medications review
- AE review. If significant adverse events have been reported, these will be clinically followed in accordance to the instruction of the study physician

- Samples taken +/- 40 mins before or after VMMC as follows:
  - Urine for chlamydia and gonorrhoea assay (self-taken)
  - Urine (5 mLs) for PK analysis (self-taken)
  - Blood sample (60mLs) for RPR, PK and PD analysis
  - Optional rectal swab for PK analysis (self-taken or researcher taken)
- Samples taken immediately before VMMC as follows:
  - One urethral swab for cytokine analysis will be done immediately prior to cleaning and preparation of the penis (researcher-taken)
  - One Diogene swab of the Coronal Sulcus at MMC for microbiome analysis (researcher-taken)

VMMC will be carried out according to local guidelines and the time of removal of foreskin will be accurately recorded. In brief, a sterile surgical pack containing all the necessary consumables is opened for each participant, after physical examination of the penis to ensure that no anatomical abnormalities or evidence of STI are found. A nurse instils local anaesthetic around the base of the penis and using povidone iodine solution, cleans and prepares the penis for surgery. Approximately 10-15 minutes later, the operator (either a doctor or clinical associate) will test anaesthesia, and if complete, will clamp the foreskin just above the glans and excise of the distal foreskin immediately thereafter. Four stay sutures at each quadrant of the wound are placed by the operator after using diathermy to stop any bleeding points; the intervening surgical wound is then sutured. If the forceps guided method is not indicated, a dorsal slit circumcision will be done. The wound is dressed and once the participant feels up to it, he walks to the recovery room and waits there for an hour. Analgesics are dispensed together with wound care instructions. Men will be not advised to resume intercourse until six weeks after circumcision and to use condoms. The resected foreskin will be transferred on wet ice or a cool pack to the laboratory immediately. The foreskin must arrive at the laboratory within two hours of VMMC.

#### *Exit survey and procedures*

At the VMMC visit or the final study visit (post VMMC), all participants will complete a self-or interviewer administered short exit survey using the electronic database, ODK and/or iDatafax. Questions will focus on motivation and concerns for trial participation, sexual behaviour, PrEP acceptability (for participants who took PrEP) and clinical trial experience. The survey will take approximately 5 minutes to complete. The exit survey will be translated into the main local

languages of each country (South Africa: Zulu, Sesotho; Uganda: Luganda).

#### *In-Depth Interview procedures*

In those consenting, IDIs will be conducted to explore in-depth perspectives and attitudes towards HIV risk, acceptability of young people in a PrEP clinical trial and use/perceptions of PrEP. These will take place at an arranged time 1 to 4 weeks following VMMC. Young men aged 13-24 years (n=20-25 per site), who participated in the clinical trial and clinical trial health care providers (n=3-5 per site) will be asked to take part in a once-off IDI. IDIs will take place on the day of the VMMC visit or on the day of the final study visit (post VMMC). Interviews will be conducted face-to-face by trained research assistants in a private room at the research sites. Interviews will be audio-recorded and conducted in the country's local languages and English, as preferred by participants. IDIs will last for approximately 30 minutes and separate participant consent or assent for IDIs and audio-recording will be obtained prior to the interview. Parental/guardian consent will be obtained for participants younger than 18 years. Additionally, parent/guardian consent for audio recording will be completed.

#### *Semi-structured interview guide for IDIs*

A semi-structured interview guide will be used for IDIs with trial participants and health care providers to investigate a number of questions including adolescents' attitudes and experience of the clinical trial conduct, experience/perceptions of PrEP use, sexual behaviour, and to explore how prevention interventions can be improved to recruit and retain participants in clinical trials. The interview guide will be pilot tested among the adolescent and adult community advisory boards in each country.

### **7.1.5 Exit safety visit after VMMC**

- Physical / genital exam if clinically indicated
- Concomitant medications review
- AE review. If adverse events have been reported, these will be clinically followed in accordance to the instruction of the study physician.

## **7.2 Laboratory Tests**

### **Safety and eligibility samples**

All results will be recorded on the eCRF. The investigator must review, sign and date the laboratory

results/reports, comment whether any abnormal values are clinically significant and record any clinically relevant changes occurring during the study in the adverse event section of the eCRF.

**- HIV-1 risk assessment and HIV-1 testing**

Site personnel will assess volunteers for past and current risk of HIV infection. Additionally, site personnel will perform pre-HIV test counselling. Two rapid HIV tests performed according to manufactures specifications, that both are clearly negative will be used as evidence of absence of HIV infection. In the event of a volunteer being diagnosed HIV-1 positive at screening they will immediately be referred to the nearest facility with a copy of their results and a referral letter for further counselling and care.

**- STI screening**

First-catch urine samples (5ml) will be analysed locally for gonorrhoea and chlamydia. In the event of an infection is detected, participants will be recalled for treatment according to local guidelines and contact tracing carried out.

**- Serum haemoglobin**

A blood sample will be taken and sent to the routine laboratory for analysis.

### **7.3 Clinical Research sample processing**

Clinical samples taken at VMMC visit must be transferred immediately to the local laboratory so that they are received within 2 hours of sample collection. The methods for sample collection and packaging for transfer are described in the operations manual.

#### **Laboratory Research Sample analysis**

It is not possible for laboratories to be blinded to the participants' arm allocation due to the different laboratory experiments carried out on controls versus cases as well in vitro dosing of FTC-TDF versus FTC-TAF. The time of day a sample is received will also be dictated by study arm.

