#### 4.1.1 Primary endpoint

The primary endpoint is **non-infection of foreskin tissue with HIV** (in the lab) **at 15 days** following ex vivo challenge. This is because we wish to demonstrate the potential protective effect of the drugs.

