## **7.4 End point Sample Analysis**

**a. Ex vivo challenge of foreskin tissue and PBMCs**

Quantification of protection from HIV-1 infection in foreskin tissue and PBMCs will be initially carried out in local laboratories. In brief, foreskin explants will be challenged or not (for negative background control tests) *ex vivo* with HIV-1BaL at two titers; a high titer normally used in pre-clinical assays in the laboratory and a low titer trying to mimic *in vivo* levels. *Ex vivo* challenge will be performed using a non-polarized system by submerging the tissue explant in 200 µl of

virus diluted at the appropriate titer. Following 2 h of incubation, explants will be washed with PBS to remove unbound virus and transferred to a fresh culture plate. Tissue explants will then be cultured for 15 days and maintained by harvesting approximately two-thirds of culture supernatant at days 3, 7, 11 and 15, and refeeding the cultures with fresh medium. The extent of virus replication in tissue explants will be determined by measuring the p24 antigen concentration for HIV-1 in supernatants at each harvest time point with antigen-specific ELISA. The supernatant fluid collected from the culture supernatants will be stored and subsequently analysed for HIV infection at Imperial College London. Interim analyses after 30% and 60% recruitment will confirm continued validation of assays and whether recruitment needs to be extended in any arm.

*Ex vivo* dosing of foreskin explants with FTC-TDF or FTC-TAF will be used to i) mimic the postcoitus dosing in the IPERGAY trial; and ii) evaluate the time frame for initiating PEP with FTC- TDF or FTC-TAF. In the first case, to mimic IPERGAY, foreskin samples obtained from CHAPS participant who will have received one or two pills of FTC-TDF or FTC-TAF, will be dosed by submerging the explant in 200ul of drug diluted at the appropriate concentration, 18hrs after *ex vivo* viral challenge.

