## **14. Direct Access to Source Data and Documents**

Every effort will be made to protect participant privacy and confidentiality. Study-related information will be stored securely at the study site. All participant information will be stored in lockable file cabinets in areas with access limited to study staff. Data collection, administrative forms, laboratory specimens, and other reports will be identified by a coded number only to maintain participant confidentiality.

Databases will be secured with password-protected access systems. Forms, lists, logbooks, appointment books, and any other listings that link PID numbers to other identifying information will be stored in a separate, locked file in an area with limited access. Clinical information will not be released without written permission of the participant or participant's parent/legal guardian, except as necessary for monitoring by:

- Authorized study representatives
- In country Health Regulatory Authorities
- Relevant Research Ethics Committees
- Other Regulatory Agencies
- Monitors and Auditors

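### Section 7.3 rules out blinding for all laboratories, but its reasons concern only fresh-tissue handling; the central p24 read that decides the primary endpoint could be masked

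*Protocol*

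**What the plan says.** The trial is open label, and Section 6.4 says that participants and research team will know the allocation. Under Laboratory Research Sample analysis, Section 7.3 extends this to the laboratories: "It is not possible for laboratories to be blinded to the participants' arm allocation". Two reasons are attached, "due to the different laboratory experiments carried out on controls versus cases as well in vitro dosing of FTC-TDF versus FTC-TAF", and a third follows: "The time of day a sample is received will also be dictated by study arm".

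The primary endpoint in Section 4.1.1 is "non-infection of foreskin tissue with HIV" at day 15. Section 7.4a describes the assay as "measuring the p24 antigen concentration for HIV-1 in supernatants at each harvest time point with antigen-specific ELISA". The same section says that quantification begins in the local laboratories, and that supernatant is "stored and subsequently analysed for HIV infection at Imperial College London". It also provides for looks after 30% and 60% recruitment, which may lead to extended recruitment in an arm.

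Section 9.2 bases the primary comparison on Groups A to D without post-exposure drug. Section 13 reserves accumulating data by randomised group to the IDMC. Section 14 says that "laboratory specimens, and other reports will be identified by a coded number only", giving confidentiality as the purpose.

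**The concern.** Because the oral dosing is open label, reading the outcome is the main step at which masking is still possible. Section 7.3 gives that up for every laboratory, while the reasons offered describe only the bench that receives and doses tissue. Followed as written, the infected/non-infected call, the decision to repeat an assay and the decision to drop a well can all be made by someone who knows the arm.

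The local laboratories also make the first quantification. Staff who know the allocation could therefore see p24 results build up by arm, which fits poorly with Section 13. An analysis plan cannot restore masking once the plates have been read.

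**Working it through.** **1. The plan's own numbers.** 9 arms × 16 = 144 men; 9 × 8 = 72 per country; 2 × 16 = 32 per pooled group. These agree with Section 9.1. No alpha, power or effect size is given, so there is no power figure to check.

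**2. Each stated reason against the path of the endpoint.** The path is tissue receipt, cutting, viral challenge, any in vitro dosing, culture, harvest at days 3, 7, 11 and 15, storage, ELISA, then the call.

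| Reason in Section 7.3 | Step it affects | Does it prevent a masked read of stored supernatant? |
|---|---|---|
| Different experiments on controls | Cutting, dosing and culture at the site | No, if each aliquot has its own code |
| In vitro FTC-TDF v FTC-TAF | Dosing at the site | No. The wells for the primary comparison (A-5-0 to D-21-0 in Table 2.1) get no in vitro drug, nor does the X-0 reference |
| Time of receipt | Receipt at the site | No. The central reader receives stored aliquots |

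**3. Whether the existing labels mask anything.** They do not. Section 6.4 prints study IDs on the randomisation envelopes, and Section 7.1.2 logs participant ID with arm. Controls would also stand out by their number of conditions. Tables 2.1 and 2.2 give a control man 1 + 2 + 8 = 11 conditions (no drug, two drugs at 18 hours, two drugs at four further times), assuming that the no-drug condition is shared between the tables. A man in Arms 2 to 9 has 2. Codes must therefore be per aliquot and separate from the study ID.

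**4. Scale of one call.** 1/32 = 3.1 percentage points in a pooled PrEP group; 1/16 = 6.25 points in the control group.

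**5. Illustration (assumed inputs, not in the protocol).** Let both groups have true non-infection proportion p, and let a share b of infected results be called favourably in one group only. The apparent proportion there is p₂ = p + b(1 − p), so the spurious difference is b(1 − p). The 95% half-width for 32 v 32 is 1.96 × √[p(1 − p)/32 + p₂(1 − p₂)/32].

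| p | b = 10%: spurious difference (half-width), points | b = 20%: spurious difference (half-width), points |
|---|---|---|
| 0.3 | 7.0 (23.1) | 14.0 (23.4) |
| 0.5 | 5.0 (24.4) | 10.0 (24.3) |
| 0.7 | 3.0 (22.1) | 6.0 (21.7) |

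In every case shown, the spurious difference is smaller than the half-width.

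**The case against.** The local bench cannot be fully blinded, and that part of Section 7.3 stands. Several stronger readings are tempting, but the document does not support them.

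- *The interval could be hidden from the bench.* Arms differ by 5 v 21 hours between last dose and surgery (Table 1), tissue must arrive within two hours (Section 7.1.4), and arrival time follows the arm. A handling code would not conceal this.
- *Every laboratory read could be masked.* Table 4 lists TAF, TFV and FTC. TAF is given only in Arms 6 to 9 and controls take no drug, so a drug-level result itself points to the drug.
- *The coded numbers in Section 14 already provide a mask.* They serve confidentiality, and the IDs can be traced to arm.
- *The endpoint is read only centrally.* Section 7.4a puts the first quantification in the local laboratories, where the stated reasons do apply. The protocol does not say which read is the endpoint of record.
- *The results will be materially biased.* ELISA gives a number, the analysis is descriptive and also uses p24 level, slope and AUC, and Section 9.1 says that the study is not powered to compare the four treatment groups. Nothing in the protocol shows that any call would be swayed.

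It is also fair to say that plate layout and repeat rules often sit in a laboratory manual or SAP, which are not shown. A masked read may be described there. If so, it conflicts with the flat statement in Section 7.3, which still needs correcting.

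**Conclusion.** The point holds for the reading of the endpoint, not for tissue processing. None of the three reasons prevents a masked central p24 ELISA on recoded supernatant, and the protocol provides for no such read.

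The expected bias is modest. It is confined mainly to borderline calls, repeats and excluded wells, at 3.1 points per changed call in a group of 32 and 6.25 in the control group. Under the assumed misreading of 10%, the spurious difference is 3 to 7 points against a half-width of about 22 to 24. At 20% it is 6 to 14 points. These shares are assumptions to show scale, not estimates.

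The conclusion assumes that the central reader can work from aliquots alone, without the allocation log, and that the central result can serve as the endpoint. Decisions at the local bench, such as discarding a damaged explant during culture, would remain unmasked. This is a cheap improvement worth making, not a flaw that invalidates the design.

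**What to change.** 1. Reword Section 7.3 so that the statement covers only receipt, cutting, challenge and in vitro dosing of tissue at the local laboratories.
2. In Section 7.4a, name the central p24 read as the endpoint of record and limit the first local quantification to assay monitoring.
3. Give each supernatant aliquot an arm-neutral code distinct from the study ID, and mix arms on each ELISA plate.
4. Fix infected/non-infected calls, repeats and exclusions before codes are linked to arm. Do this at the final analysis and at each of the 30% and 60% looks, where linkage is for the IDMC only, in line with Section 13.
5. Apply the same recoding to reads that depend on judgement, such as the microscopy counts in Section 7.4f.
6. Do not claim that the interval is hidden from the local bench or that drug-level assays are masked as to drug.

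The cost is protocol and laboratory-manual wording, relabelling of aliquots at each harvest, and a code list held by the trial statistician or data centre. No further participants or assays are needed.

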**a. Blood sample**

Plasma, CD4+ expressing cells and PBMCs will be extracted from 50mls whole blood. Ex vivo challenge of PBMCs will occur immediately. The remaining PBMCs and Plasma samples will be stored for drug level and cytokine analysis. Should there be sufficient sample remaining after the other analyses, we will also test for the presence of SARS-CoV-2 antibodies using samples

taken prior to circumcision. This was requested because of concerns relating to inflammation related to COVID-19 which may impact our primary outcome, and also high rates of asymptomatic SARS-CoV-2 infections reported in South Africa and elsewhere which may be detected on antibody testing.

